## Abstract

**Background:**

School absenteeism, including medical absenteeism, is associated with early school dropout and may result in physical, mental, social and work-related problems in later life. Especially at intermediate vocational education schools, high rates of medical absenteeism are found. In 2012 the Dutch intervention ‘Medical Advice for Sick-reported Students’ (MASS), previously developed for pre-vocational secondary education, was adjusted for intermediate vocational education schools. The aim of the study outlined in this paper is to evaluate the effectiveness of the MASS intervention at intermediate vocational education schools in terms of reducing students’ medical absenteeism and early dropping out of school. Additionally, the extent to which biopsychosocial and other factors moderate the effectiveness of the intervention will be assessed.

**Methods:**

A controlled before-and-after study will be conducted within Intermediate Vocational Education schools. Schools are allocated to be an intervention or control school based on whether the schools have implemented the MASS intervention (intervention schools) or not (control schools). Intervention schools apply the MASS intervention consisting of active support for students with medical absenteeism provided by the school including a consultation with the Youth Health Care (YHC) professional if needed. Control schools provide care as usual. Data will be collected by questionnaires among students in both groups meeting the criteria for extensive medical absenteeism (i.e. ‘reported sick four times in 12 school weeks or for more than six consecutive school days’ at baseline and at 6 months follow-up). Additionally, in the intervention group a questionnaire is completed after each consultation with a YHC professional, by both the student and the YHC professional. Primary outcome measures are duration and cumulative incidence of absenteeism and academic performances. Secondary outcome measures are biopsychosocial outcomes of the students.

**Discussion:**

It is hypothesized that implementing the MASS intervention including a referral to a YHC professional on indication, will result in a lower level of medical absenteeism and a lower level of school drop outs among intermediate vocational education students compared to students receiving usual care. The study will provide insight in the effectiveness of the intervention as well as in factors moderating the intervention’s effectiveness.

**Trial registration:**

Nederlands Trial Register NTR5556. Date of clinical trial registration: 29-Oct-2015.

## Background

Obtaining a basic educational degree increases the chances of finding a permanent skilled job and is associated to better health. Students who break off their education prematurely often find themselves in a more vulnerable situation with regard to developing illnesses, being unemployed and being involved in criminal activities, as compared to students who hold a basic educational degree. Reasons to drop out of school prematurely, as reported by students, vary from learning and motivation difficulties, behavioural, (mental) health problems to problems at home [1–5].

School absenteeism is often a precursor of school dropout and absenteeism in future careers [4, 6–10]. It can be divided into unexcused (truancy) and excused absenteeism. The most common form of excused absenteeism is absence due to sickness reporting or sick leave, so called medical absenteeism. Medical absenteeism is perceived twice as often as truancy among adolescent students [11]. Particularly at intermediate vocational educational schools, high rates of medical absenteeism and school dropout can be found. Of all students entering intermediate vocational education, only 50% passes on to the second year and after five years approximately 25% leaves school without a degree [12]. Investing in effective methods regarding the prevention of extensive medical absenteeism at intermediate vocational education schools is therefore relevant.

The Dutch Youth Health Care (YHC) system offers preventive health care for children and adolescents between 0 and 18 years old. It aims to foster the optimal trajectory for growth and development in children and to provide anticipatory guidance to prevent negative outcomes later in life [13]. In general, the YHC system does not focus actively on students with extensive medical absenteeism. The current policy of most intermediate vocational education schools does not include an active identification of students with extensive absenteeism and referrals to YHC professionals are limited [14, 15]. Because of the high rate of medical absenteeism at intermediate vocational education schools and the complex underlying problems, however, the YHC system could play an important role in addressing medical absenteeism [16–20].

In 2012, the Medical Advice for Sick-reported Students (MASS) intervention was developed [19] to address medical absenteeism more actively within students attending pre-vocational secondary education, the school level preceding intermediate vocational education. The aim of the MASS intervention is to limit medical absenteeism by arranging appropriate care, educational adjustments and adequate support for students [21]. The intervention focuses on the factors associated with extensive medical absenteeism: somatic, mental and physical complains [9, 22–25], poor lifestyle [11] and psychological, family and social problems of sick-reported students [9]. The schools and the YHC professionals collaborate directly within the MASS intervention to design and monitor a management plan that aims to optimize students’ health and maximize students’ participation in school activities [19, 25] In an effect study Vanneste et al. found a reduction of 15.1% in medical absenteeism among pre-vocational secondary education school students after implementing the MASS intervention [19].

As students in pre-vocational secondary education schools often continue their education at intermediate vocational education schools, medical absenteeism might be associated with the same determinants in both groups of students. Despite potential similarities between intermediate vocational education and pre-vocational secondary education students, there are also clear differences that need to be taken into account in designing interventions. Students in intermediate vocational education schools, for instance, are generally aged between 15 and 25 years old. Furthermore, the level of medical absence is often larger at intermediate vocational education schools and its nature is often more complex due to underlying biopsychosocial factors and financial problems. As a result, the MASS intervention has been adapted for intermediate vocational education schools and is currently being applied at several schools in the Netherlands [26–28]. However, evidence for its effectiveness is thus far lacking.

The aim of this study is to evaluate the effectiveness of the MASS intervention at intermediate vocational education schools, with a focus on the efforts of the YHC professional, in terms of reducing students’ medical absenteeism and early dropping out of school. In addition, we will assess to what extent biopsychosocial and other factors may influence the effect of the intervention.

## Methods/Design

### Study design

A controlled before-and-after study with a follow-up period of 6 months will be conducted. Students with extensive medical absence attending schools in which the MASS intervention has been implemented (intervention group) are compared to students attending schools in which the MASS intervention has not been implemented (control group).

The Medical Ethical Committee of Erasmus University Medical Centre Rotterdam has declared that the Medical Research Involving Human Subjects Act (also known by its Dutch abbreviation WMO) does not apply to this research protocol and issued a declaration of no objection (i.e. formal waver) for this study (MEC-2015-614). Therefore, the study can be carried out without further approval by an accredited research ethics committee.

### Setting

This study will be conducted in the Dutch setting of intermediate vocational education schools and will focus on students aged between 16 and 25 years. In the Netherlands, students under the age of 18 leaving lower secondary school have to continue a higher general secondary education or enter one of the five intermediate vocational education programs: technology, economics, agricultural, personal/social services or health care. The intermediate vocational education schools prepare students for a specialized trade by developing a particular expertise. After graduating from an intermediate vocational education school one can enter higher vocational education or start working [29].

### Participants

#### Youth health care organizations, schools and youth health care professionals

This study will be conducted in the Dutch regions of Amsterdam, Utrecht, West Brabant and Rotterdam. School recruitment will be organized in collaboration with three YHC organizations associated to the regions of Amsterdam, Utrecht and West Brabant. The YHC organization in Rotterdam will not be involved in the study as schools in this area have not yet implemented the MASS intervention and will therefore be allocated to the control group.

YHC organizations invite the intermediate vocational education schools to participate in the study. Schools that agree to participate will subsequently be visited by the researchers. It is expected that a total of 12 schools will participate. The allocation of the schools will be based on their current policy. Schools will be classified as an intervention school (IS) or as a control school (CS) based on their current use of the MASS intervention.

All YHC professionals of participating intervention schools will be offered a training in the MASS intervention at the start of the study.

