#### Covariates

The covariates are chosen based on comparison of baseline characteristics of intervention and control students. Demographic information regarding the participating students is collected at baseline including ethnicity, SES score, attending school, educational level, and parenthood. Information on a number of known risk factors for school absenteeism are collected at baseline and during follow-up, including age, gender, smoking status, alcohol consumption (abstainer, up to >7 servings/week) and drugs abuse (abstainer, soft drugs, and hard drugs). Biopsychosocial problems concerning medical, physical, emotional, and psychiatric problems (e.g. depression, anxiety, ADHD), housing, financial problems and contacts in criminal justice are included as covariates. Level of physical activity is assessed at baseline and follow-up.

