### Statistical analyses

In order to evaluate effect of the effect of the intervention the scores on outcomes of both groups measured during follow will be compared, adjusted for baseline findings. For continuous outcome measures such as duration of the medical absenteeism and psychometric test results (multiple) linear regression analyses will be applied. Dichotomous outcomes, such as progressing into the next year or obtaining a basic educational qualification degree, will be evaluated by using a multiple logistic regression analysis.

The research condition will be included as an independent variable. Baseline values of the outcomes are added to the model as covariates. As students are clustered within school locations multilevel analyses will be applied.

Potential moderation of intervention effects by gender, family situation, ethnicity, psychosocial and psychiatric problems (depression, drug abuse, ADHD) is explored by adding an interaction term to the regression models. Stratified analyses will be performed when significant interactions (*p* < 0.10) are observed.

Experiences of students and YHC professionals with the different elements of the MASS intervention as performed by YHC professionals will be evaluated by performing descriptive analyses.

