## Discussion

Medical absenteeism is positively associated to early school dropout and may result in physical, mental, social and work-related problems later in life. The aim of the MASS intervention is to limit the medical absenteeism of students by arranging appropriate care, educational adjustments and adequate support [19, 21]. This paper describes the design of a controlled before-and-after study, which aims to evaluate the effectiveness of the MASS intervention as well as its contributing factors and interfering factors among intermediate vocational education school students.

It is hypothesized that implementation of the MASS intervention and incorporating a referral to a YHC professional is effective in terms of reducing medical absenteeism. Results of this study will show whether the YHC professional added value in the MASS intervention. Moreover, the study will provide insight in which factors contribute and/or moderate to the intervention’s effectiveness and may provide useful suggestions for improvement.

A strength of this study is that it will be conducted in the daily setting schools and YHC practice, which will facilitate future implementation. The participating schools and YHC professionals cover the urban and rural areas of the Netherlands, which will support the generalizability of our findings. Nevertheless, the schools and students are not randomized which can result in differences between the groups. We have tried to minimize this potential effect by correcting for potential confounders. Another strength is that we look at the extent to which the MASS intervention is applied by de YHC professional and gain insight into the care provided by the school to the individual students.

As the MASS intervention had already been implemented at the intervention schools, we could not capture strict criteria for referral to the YHC professional. The criteria for referral to a YHC professional were determined by each individual school which is in line with the MASS protocol, which may result in a variety of used criteria. On the other hand, this will give a realistic approach of the effects of the implementation of the MASS intervention. Also, the MASS-protocol requires great commitment of the schools to identify and refer students to YHC professionals [43]. It is therefore questionable how many students eventually will be identified and/or referred to the YHC professional.

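### Rotterdam can supply only control schools and no within-region comparison is stated, so a residual regional difference can mix with the MASS effect in either direction

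*Protocol article*

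**What the plan says.** On recruitment and allocation (Participants, first subsection): "This study will be conducted in the Dutch regions of Amsterdam, Utrecht, West Brabant and Rotterdam". The youth health care (YHC) organizations of the first three regions help to recruit schools. Rotterdam's is not involved, because "schools in this area have not yet implemented the MASS intervention and will therefore be allocated to the control group". The general rule is: "Schools will be classified as an intervention school (IS) or as a control school (CS) based on their current use of the MASS intervention". On numbers: "It is expected that a total of 12 schools will participate". The text gives no split by region or by arm; the flow chart was not visible in the copy I read.

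On adjustment (Covariates): "The covariates are chosen based on comparison of baseline characteristics of intervention and control students". The demographic items are "collected at baseline including ethnicity, SES score, attending school, educational level, and parenthood". Known risk factors and biopsychosocial problems follow. Region does not appear.

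On the model (Statistical analyses): "Baseline values of the outcomes are added to the model as covariates". Clustering is handled by multilevel models at the level of school location. The moderators to be explored are gender, family situation, ethnicity, and psychosocial and psychiatric problems. No region term, region stratum or analysis without Rotterdam is stated.

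The Discussion admits that schools and students are not randomized and answers: "We have tried to minimize this potential effect by correcting for potential confounders". It mentions the spread over urban and rural areas only as support for generalizability.

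**The concern.** One of four regions can never contribute an intervention school. Whatever sets Rotterdam apart falls on the control side only: recording practice in school registers, the usual support available, local conditions. A random intercept for school location models the scatter between schools. It does not remove a systematic difference in regional means between the arms.

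At stake is what the result may be called. If the arms differ at T1, the stated analysis gives the reader no means of judging how much of the difference comes from MASS and how much from Rotterdam. If they do not differ, a real effect may have been offset by lower absence in Rotterdam.

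**Working it through.** **1. The plan's own figure.** Inputs from Power considerations: 120 complete students per arm, intraclass correlation 0.10, 15 per class, SD 30 h, one-sided alpha 0.05, power 0.80.

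- Design effect = 1 + 14 × 0.10 = 2.4; effective n = 120 / 2.4 = 50 per arm.
- SE of the arm difference = 30 × √(2/50) = 6.0 h.
- Detectable difference = 6.0 × (1.645 + 0.842) = 14.9 h. The stated 15 h is reproduced.

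**2. Bias formula (assumptions).** Let f be Rotterdam's share of the controls and d the amount by which T1 absence in Rotterdam differs from the other regions. Take the other three regions as equal on average in both arms, and schools as equal in size.

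- Without baseline adjustment: bias = f × d, SE = 6.0 h.
- With baseline adjustment at correlation ρ: bias = f × d × (1 − ρ), SE = 6.0 × √(1 − ρ²). This supposes that the regional difference is stable and fully visible at T0, which is favourable to the plan.
- One-sided false-positive rate = 1 − Φ(1.645 − bias/SE).

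**3. Illustration.** Six control schools with 3 in Rotterdam (f = 1/2) and d = 6 h (0.2 SD):

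- Unadjusted: bias 3 h; 1 − Φ(1.645 − 0.50) = 12.6%.
- Adjusted, ρ = 0.5: bias 1.5 h, SE = 6.0 × √0.75 = 5.2 h; 1 − Φ(1.645 − 0.289) = about 9%.

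The range over other assumed values:

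| f | d (h) | Bias, unadjusted (h) | False positive | Bias, ρ = 0.5 (h) | False positive |
|---|---|---|---|---|---|
| 1/6 | 5 | 0.8 | 6.6% | 0.4 | 5.9% |
| 1/3 | 10 | 3.3 | 13.8% | 1.7 | 9.3% |
| 1/2 | 10 | 5.0 | 20.9% | 2.5 | 12.2% |
| 1 | 6 | 6.0 | 26% | 3.0 | 14% |
| 1 | 15 | 15 | 80.4% | 7.5 | 42.0% |

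**4. The other direction.** If absence in Rotterdam is 6 h lower and f = 1/2, a true 15 h effect is estimated as 12 h on average. Unadjusted power falls from Φ(15/6.0 − 1.645) = 0.80 to Φ(12/6.0 − 1.645) = Φ(0.355) = 0.64.

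**5. What the stated adjustment reaches.**

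- Baseline absence removes part of a stable regional difference. Three things limit this. Students enter only after crossing an absence threshold, which compresses differences at T0. The Discussion says MASS was already in place at intervention schools, so T0 is not a clean value from before the intervention. And progression to the next year or gaining the basic qualification, a primary outcome, has no natural baseline value.
- SES, ethnicity and educational level may carry some regional difference. They need not capture how a school registers absence or what support it offers.
- School attended, as a fixed covariate, cannot help, because each school belongs to one arm only.

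**6. Precision of a restricted analysis.** Assume 12 schools of 20 complete students (240/12), SD 30 h, ICC 0.10. The variance of a school mean is 90 + 810/20 = 130.5.

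- All 6 + 6 schools: √(130.5 × (1/6 + 1/6)) = 6.6 h. This exceeds the 6.0 h of step 1 because it uses 20 students per school instead of 15 per class.
- 3 Rotterdam schools dropped: √(130.5 × (1/6 + 1/3)) = 8.1 h. A region fixed effect gives the same value if each remaining region holds 2 intervention schools and 1 control school.
- Chance difference between the full and restricted estimates: SE about √(8.1² − 6.6²) = 4.7 h.
- All 6 control schools in Rotterdam: no region holds both types, and the effect cannot be estimated with a region term.

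**The case against.** The strongest reply has four parts.

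First, a reader might infer that every Rotterdam difference passes straight into the condition coefficient and that the model cannot correct for it. The text does not support that: baseline outcome values are in the model, and student covariates may take up part of the rest. This stands. It lowers the illustrative rates for 3 h and 6 h of unadjusted bias from 12.6% and 26% to about 9% and 14% at an assumed correlation of 0.5. It does not bring them to 5%.

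Second, a reader might infer that region and condition are nearly the same variable. That is not shown either. Nothing limits the invitations in Amsterdam, Utrecht and West Brabant to schools that use MASS, and schools there are classified by current use. Those regions may supply control schools, and only Rotterdam's share carries the bias. Nor is region the only confounder created by allocation on current policy: adopting schools may differ from non-adopting schools anywhere.

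Third, a restricted analysis is not clearly less biased. Non-adopters in regions where MASS is in use may be more self-selected and may share a YHC organization with MASS schools. This stands, and it is a reason to report the analysis beside the main estimate and not in its place.

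Fourth, sensitivity analyses are often left to an analysis plan, and the non-random design is openly admitted. True in general. But this article itself fixes the allocation rule, the candidate covariates, the clustering level and the moderators, and offers confounder correction as the remedy. Followed as written, it leaves out a difference between the arms that its own allocation rule creates.

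**Conclusion.** The point holds as a residual risk of unknown size. Rotterdam is control-only, and nothing in the stated analysis adjusts for region or compares schools within a region. Whatever regional difference survives baseline and covariate adjustment can be mixed with the MASS effect, upward or downward.

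The illustrative rates rest on an assumed arm split, an assumed Rotterdam share, an assumed regional difference and an assumed baseline correlation; none is in the document. They show that a moderate difference would matter. They do not show that one exists. The change should be made, because it is cheap and it settles in advance what may be attributed to MASS.

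**What to change.** - Keep the main analysis as planned.
- Pre-specify a sensitivity analysis of the primary outcomes, restricted to regions that hold both intervention and control schools, with region as a fixed effect.
- Report its estimate and confidence interval beside the main estimate, with the number of intervention and control schools per region. Do not use the comparison as a pass/fail rule: with 3 of 6 control schools dropped, chance alone separates the two estimates with an SE of about 4.7 h.
- State beforehand that if no or very few control schools lie outside Rotterdam, MASS and region cannot be separated and the difference will not be attributed to MASS alone. Define very few before the outcome data are seen.
- Name the Rotterdam allocation as a specific limitation in the Discussion.

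The cost is one additional model per primary outcome and one small table. The downside is precision: an SE of about 8.1 h against 6.6 h if 3 of 6 control schools are dropped. It is therefore a sensitivity analysis and not a replacement.
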